Specific monitoring will be performed for retinal toxicity, which is a recognized side effect of ethambutol and has been observed in some animal species after prolonged dosing of moxifloxacin (though not reported in clinical trials or post-marketing surveillance of moxifloxacin). Monitoring for retinal toxicity will consist of visual acuity and color vision testing per standard site practice. Laboratory monitoring will consist of a CBC, serum AST, bilirubin, and creatinine, and will be obtained at 2, 4, 6, 8, and 12 weeks. Because significant cardiotoxicity has not been observed among the over 10 million patients treated with moxifloxacin after its approval and is not associated with the duration of treatment in animal models, electrocardiographic monitoring will not be done during this study.

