### Drug-drug interactions

Interaction studies have been performed with moxifloxacin and theophylline[68], warfarin, digoxin, probenecid[69], ranitidine, glyburide[70], iron[71], calcium supplements[72], sucralfate[73], and antacids[74]. Only a few clinically significant interactions have been described. All fluoroquinolones can bind to multivalent cations (esp. Fe+3, Al+3, and Mg+2, but not Ca+2], with resultant substantial (40-60%) decreases in absorption when taken concurrently. Moxifloxacin should not be administered at the same time as antacids containing magnesium and/or aluminum, sucralfate, antidiarrheals that contain kaolin, or iron and/or zinc containing medications or supplements.

Rifampin induces the activity of the phase II enzymes glucuronosyltransferase and sulphotransferase [75]. Interaction studies between rifampin and moxifloxacin have not been performed. However, because glucuronidation is a minor pathway in moxifloxacin metabolism (accounting for approximately 20% of total hepatic metabolism), a significant interaction between rifampin and moxifloxacin is unlikely.

Tolerability

As a class, fluoroquinolones are considered to be safe and relatively free of serious adverse effects[76]. The safety and efficacy of moxifloxacin for the treatment of community acquired bacterial infections has been extensively studied, and the drug is approved in the U.S. as a 10-day course of treatment for upper and lower respiratory tract infections.

In the usual daily doses of 400 mg/day, moxifloxacin is well tolerated. Expected minor adverse events have occurred with a frequency similar to that for other fluoroquinolones in similar populations. Gastrointestinal adverse effects are the most common, and they include nausea (7%), diarrhea (6%), dizziness (3%), abdominal pain (2%), vomiting (2%), dyspepsia (1%), and taste perversion (1%). There are no current reports of hepatitis, although abnormal liver function tests have been noted in 1% of patients.

Of note, fluoroquinolones are generally used short-term for acute conditions. However, fluoroquinolones have been found to be safe and effective in long term use for chronic infections such as osteomyelitis, prostatitis, or chronic urinary tract infection, or skin and skin structure infections[76, 77]. In addition, Valerio et al. found that the combination of moxifloxacin, isoniazid, and rifampin given for 6 months was well tolerated[32].

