### To compare the safety and tolerability of the moxifloxacin regimen to that of the isoniazid regimen

### To determine the time to culture-conversion of the moxifloxacin regimen and the isoniazid regimen using data from 2-, 4-, 6-, and 8-week cultures

- To compare the proportion of patients with any Grade 3 or 4 adverse reactions
- To compare adverse events and 2-month culture conversion rates among HIV-infected patients vs. HIV-uninfected patients
- To compare the rates of treatment failure of the moxifloxacin regimen and the isoniazid regimen
- To determine whether there is delayed toxicity attributable to moxifloxacin (toxicity that becomes evident after the 8 weeks of moxifloxacin therapy)
  1. Study Endpoints

**Sputum culture conversion** – sputum culture obtained at the end of the intensive phase of therapy has no growth of *M. tuberculosis*. The end of the intensive phase of therapy will be defined by completion of the required number of directly-observed doses (as defined in Section 3.1), rather than by a specific number of weeks of therapy. In order to assure that each subject will be evaluable for the primary endpoint, two sputum cultures will be obtained at the end of the intensive phase of therapy. These two cultures must have been obtained (a) 0-7 days after the completion of the intensive phase of therapy (preferably, one on the day of completion and one within 7 days of completion), and (b) prior to receiving more than one dose of continuation phase therapy. Sputum culture conversion will be based on the results of both sputum cultures performed at the end of the intensive phase of therapy.  **Both sputum cultures, if evaluable, should be negative for *M. tuberculosis* in order to conclude that sputum culture conversion was achieved.** Sputum cultures that are overgrown by bacteria and/or yeast will be considered unevaluable. Subjects who are unable to produce a specimen for sputum culture despite an attempt with sputum induction will be considered to have had a negative culture on that date.

**Safety and tolerability endpoints** – the primary endpoint for the analysis of safety and tolerability will be the proportion of patients who discontinue the assigned study regimen for any reason. Other aspects of safety and tolerability that will be assessed as secondary endpoints include mortality, the occurrence of Grade 3 and 4 toxicities and the rate and types of toxicity thought related to study drug by the investigator.

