All symptoms and laboratory findings will be graded according to severity using the modified National Cancer Institute Common Toxicity Criteria (Appendix E). For the purposes of this study, pregnancy will be reported on the Adverse Event Form. All pregnant patients will be taken off study therapy and treated using the ATS/IDSA/CDC guidelines for tuberculosis treatment during pregnancy. Women who become pregnant will continue to receive scheduled follow-up, not receive additional x-rays unless clinically indicated, and be classified as being on a non-study regimen. The outcome of the pregnancy will be reported on the Adverse Event Follow-up Form.

- 1. Adverse event reporting

An adverse experience is defined as any unintended or abnormal clinical observation that is not of benefit to the patient. The adverse experiences that must be reported on an Adverse Event Form include: pregnancy, new medical diagnosis, grade 3 or 4 toxicity (potentially medication-related or other causes), study drug discontinuation, medication side-effects that are grade 3 or 4, and serious adverse events (defined in next paragraph). At the time of enrollment, if the patient already has a medical diagnosis whose signs or symptoms worsen during the study to a Grade 3 or 4, this is an adverse event that must be reported.

A serious adverse event (SAE) is defined as any experience that is fatal or life-threatening, is persistently or significantly disabling (as determined by the principal investigator), requires inpatient hospitalization, or prolongation of hospitalization, is a congenital anomaly, or overdose of study drugs. Any Grade 4 toxicity is considered an SAE.

The study drugs are moxifloxacin, ethambutol, isoniazid, rifampin, and pyrazinamide. The most common adverse effects associated with the study drugs are specified in Section 2.2 - "Study Drugs". The investigator is responsible for monitoring all adverse events that are observed or reported during the study, regardless of whether they are related to study drugs.

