For other grade 4 toxicities, the study drugs will be temporarily held and may be restarted or permanently stopped at the discretion of the investigator. Toxicities graded 3 or 4 by the Common Toxicity Criteria and occurring during study therapy will be documented on the Adverse Event Form, according to the criteria described in the next three sections. The maximum level of toxicity reached will be clearly indicated.

- 1. Criteria for discontinuation of study drugs

Certain events or conditions may necessitate temporary or permanent discontinuation of the study medication. Patients who experience such events or conditions, however, will still be "on study" and will be followed until study completion. Any patient for whom the study medication is temporarily discontinued will be restarted on study medication as soon as possible. Study regimens will be discontinued and non-study regimens will be used with continued study followup for patients who fail to respond to study therapy either clinically and/or bacteriologically, for patients in whom treatment-emergent drug toxicity warrants discontinuation of study therapy, and for patients who become pregnant. If study drugs are permanently discontinued, further antituberculous therapy may be administered at the investigator's discretion. These patients will be followed in the study for a maximum of 6 months of TB treatment, according to the guidelines and time-points established in the protocol, starting from the date of initiation of Study 28 intensive phase treatment.

- 1. Criteria for temporary discontinuation of study therapy
- Development of a toxicity that, depending on its nature and severity, requires temporary discontinuation of the study medication until the toxicity resolves as indicated in the preceding toxicity management section.
- Development of another medical condition that makes the administration of the study drug inadvisable. The decision to temporarily discontinue the study medication in this situation will be at the investigator's discretion. The period during which the patient is off study medication will be as short as clinically possible.
  1. Criteria for permanent discontinuation of study therapy
- Development of a toxicity that warrants permanent discontinuation of any study drug (refer to section on “Management of Adverse Events”).
- The patient refuses further therapy.

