| Gastric ulcer  (requires  radiographic or  endoscopic  documentation) | none | - | requiring medical management or non-surgical treatment | bleeding without  perforation,  uncontrolled by  outpatient  medical  management;  requiring  hospitalization  or surgery | perforation or bleeding, requiring  emergency  surgery |
| Also consider Hemorrhage/bleeding with grade 3 or 4 thrombocytopenia, Hemorrhage/bleeding without grade 3 or 4  thrombocytopenia. | | | | | |
| Gastritis | none | - | requiring medical  management or non-surgical treatment | uncontrolled by out-patient medical  management;  requiring  hospitalizatioor  surgery | life-threatening  bleeding,requiring  emergency  surgery |
| Also consider Hemorrhage/bleeding with grade 3 or 4 thrombocytopenia, Hemorrhage/bleeding without grade 3 or 4  thrombocytopenia.  Hematemesis is graded in the HEMORRHAGE category.  Hematochezia is graded in the HEMORRHAGE category as Rectal bleeding/hematochezia. | | | | | |

| Ileus (or  Neuro  constipation) | none | - | intermittent, not  requiring intervention | requiring non-surgical  intervention | requiring surgery |
| --- | --- | --- | --- | --- | --- |
| Mouth dryness | normal | mild | moderate | - | - |
| Mucositis  Notes: Mucositis not due to radiation is graded in the GASTROINTESTINAL category for specific sites: Colitis, Esophagitis, Gastritis, Stomatitis/pharyngitis  (oral/pharyngeal mucositis), and Typhlitis; or the RENAL/GENITOURINARY category for Vaginitis.  Radiation-related mucositis is graded as Mucositis due to radiation. | | | | | |
| Nausea | none | able to eat | oral intake significantly  decreased | no significant intake,requiring IV fluids | - |
| Pancreatitis | none | - | - | abdominal pain with pancreatic enzyme elevation | complicated by  shock (acute  circulatory  failure) |
| Also consider Hypotension.  Note: Amylase is graded in the METABOLIC/LABORATORY category.  Pharyngitis is graded in the GASTROINTESTINAL category as Stomatitis/pharyngitis (oral/pharyngeal mucositis) | | | | | |
| Vomiting | none | 1 episode in 24 hours over pretreatment | 2-5 episodes in 24 hours over pretreatment | >6 episodes in  24 hours  over  pretreatment; or  need for IV  fluids | requiring  parenteral  nutrition; or  physiologic  consequences  requiring  intensive care;  hemodynamic  collapse |

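### The related-toxicity endpoint has no grade limit, but side-effects must be reported only from Grade 3, so its rate will be incomplete and may differ between sites

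*Protocol*

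**What the plan says.** **Endpoint.** Protocol section 3.5 makes discontinuation of the assigned regimen for any reason the primary safety and tolerability endpoint. The secondary ones are mortality and "the occurrence of Grade 3 and 4 toxicities and the rate and types of toxicity thought related to study drug by the investigator". The grade qualifier belongs to the first item in that quotation. The second is defined only by the investigator's attribution. Comparing safety and tolerability is the first secondary objective in section 3.4.

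**Reporting rule.** Section 5.4 lists what must go on an Adverse Event Form. Besides pregnancy, new medical diagnoses and serious adverse events, the list contains "grade 3 or 4 toxicity (potentially medication-related or other causes), study drug discontinuation, medication side-effects that are grade 3 or 4". The end of section 5.5 gives the same threshold: "Toxicities graded 3 or 4 by the Common Toxicity Criteria and occurring during study therapy will be documented on the Adverse Event Form".

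**Other collection.** Section 5.3 has all symptoms and laboratory findings graded. Section 5.4 makes the investigator responsible for monitoring every adverse event. Section 4.1.3 has patients asked about new diagnoses and adverse events at intensive-phase visits, and Appendix D carries an adverse-event row from enrollment onward. On vision, the Synopsis says: "Monitoring for retinal toxicity will consist of visual acuity and color vision testing per standard site practice". Sections 4.1.1, 4.1.3 and 4.1.4 and Appendix D place those tests at screening, week 4, the end of the intensive phase and Month 3.

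**The concern.** An endpoint can be analysed only from events that sites are required to record with the attribute that defines it. Here that attribute is the investigator's judgement that the toxicity is related to study drug. The only instrument the protocol names for such events is the Adverse Event Form, and for side-effects its threshold is Grade 3. Below that, reporting depends on whether another trigger applies or on a site's own habit of reporting more than the list requires.

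At stake is the comparison of lower-grade tolerability. The Synopsis says the trial should assess the safety of longer moxifloxacin treatment, and the Tolerability text in the Study Drugs section expects mainly gastrointestinal effects and dizziness. A related-toxicity rate built on a Grade 3 threshold could be read as covering such effects when it covers only their severe end. If sites differ in how much they volunteer, the rate also mixes reporting practice with toxicity.

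**Working it through.** No stated figure is in dispute, so the check sets the endpoint against the reporting triggers, case by case.

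1. **Related, Grade 3 or 4.** Reportable under sections 5.4 and 5.5. These events also fall under the separate Grade 3/4 endpoint.
2. **Related, any grade, serious adverse event.** Reportable under 5.4.
3. **Related, Grade 1 or 2, amounting to a new medical diagnosis.** Reportable under 5.4, which sets no grade limit for diagnoses.
4. **Related, Grade 1 or 2, study drug stopped.** Reportable under 5.4 as a discontinuation. A temporary hold arguably counts too: sections 5.3 and 5.7 speak of temporary discontinuation, and 5.4 does not restrict its entry to permanent stops.
5. **Related, Grade 1 or 2 symptom, drug continued, no new diagnosis, not serious.** Inside the section 3.5 endpoint, but no trigger in 5.4 applies. Section 5.5 makes this an ordinary course, since drugs are in general continued at Grade 1 and held at Grade 2 only at the investigator's discretion.
6. **Visual-test decline below Grade 3, drug continued, no new diagnosis.** The result is obtained at a scheduled test, but nothing requires it to be reported as an event with an attribution.
7. **Lower-grade laboratory abnormality.** Blood count, AST, bilirubin and creatinine are measured at weeks 2, 4, 6 and 8 and at Month 3, so the values come from the schedule.

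The mismatch is cases 5 and 6.

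**How high the threshold sits.** In Appendix E, nausea with eating preserved is Grade 1 and nausea with markedly reduced intake is Grade 2. Grade 3 means "no significant intake,requiring IV fluids".

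**Scale.** The inputs are 205 patients per arm (section 3.7) and the moxifloxacin rates under Tolerability. Expected patients = 205 × rate:

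- nausea: 205 × 0.07 = 14.35, about 14
- diarrhea: 205 × 0.06 = 12.3, about 12
- dizziness: 205 × 0.03 = 6.15, about 6
- abdominal pain: 205 × 0.02 = 4.1, about 4
- vomiting: 205 × 0.02 = 4.1, about 4

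These counts should not be added, because one patient may have several effects. The protocol gives the rates in its account of moxifloxacin for bacterial infections, where the approved course is 10 days, and not for combination tuberculosis treatment. It does not say what share is below Grade 3, so no captured or missed fraction follows from the documents.

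**The case against.** The strongest reply is that the protocol collects more than the threshold suggests. The section 5.4 list is introduced as what reporting includes, so it can be read as a minimum. Its definition of an adverse experience has no grade limit, which makes the visit enquiry in 4.1.3 broad. New diagnoses, discontinuations and serious events are reportable at any grade. The case report forms are not in the document and may hold lower-grade events.

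Much of this stands, and it rules out several stronger readings that a reader might infer:

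- **That the endpoint cannot be measured at all.** Cases 1 to 4 above are captured, and some of them are below Grade 3. For the same reason the endpoint is not simply a subset of Grade 3/4 toxicity.
- **That visual changes go unrecorded.** Acuity and color vision are tested at four scheduled times, and a diagnosis of retinal toxicity would be reportable as a new diagnosis. What is missing is a rule that makes a lesser decline an attributed event.
- **That such a decline is Grade 1 and the protocol contradicts itself on handling it.** Appendix E's residual ocular category runs from mild upward and leaves the grade to judgement. Section 5.5 speaks only in general terms, and section 5.8 lets the investigator stop therapy. The toxicity text for ethambutol does not conflict with either.
- **That every Grade 2 event for which drug is held is lost.** A hold may count as a discontinuation.

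The reply does not close the gap. A minimum that sets the side-effect grade at 3 or 4 obliges no site to report lower grades. Grading and monitoring are not the same as recording with attribution. An analysis plan cannot restore events that sites were not required to report.

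**Conclusion.** The concern holds as a mismatch between a stated endpoint and a stated reporting rule. Section 3.5 sets no grade limit on related toxicity. Sections 5.4 and 5.5 require side-effects to be reported only at Grade 3 or 4, and no other instrument is named for the rest. Followed as written, the plan gives a related-toxicity rate that is incomplete below Grade 3 and may vary by site.

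The size cannot be fixed beyond the expected counts above, because the grade split is not given. The conclusion assumes that no case report form outside the document requires attributed Grade 1 or 2 events. If one does, the protocol need only say so. The consequence is confined to this secondary endpoint: discontinuation, mortality, Grade 3/4 toxicity and the scheduled laboratory and visual tests stand as planned.

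**What to change.** Make the endpoint and the reporting rule match, in one of two ways.

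**(a) Widen reporting.** In section 5.4, for the intensive phase through the Month 3 visit, add side-effects of Grade 2 or higher judged related to study drug, and any confirmed decline from screening on the already scheduled visual acuity or color vision tests. Tabulate both by arm. Word the section 3.5 endpoint as related toxicity of Grade 2 or higher, because this threshold still leaves out Grade 1 and an endpoint without a grade limit would remain unmatched. The cost is modest extra data entry, at visits and tests that already take place.

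**(b) Narrow the endpoint.** Restate it in section 3.5 as toxicity thought related to study drug that is Grade 3 or 4, is a serious adverse event, is a new diagnosis, or leads to discontinuation of study drug. This costs one sentence and no new data. The price is that the trial then makes no claim to have compared lower-grade tolerability.

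Both options concern reporting and wording only and leave clinical management unchanged.

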- Serum amino aspartate transferase (AST) activity ≤ 3 times the upper limit of normal
- Serum total bilirubin level ≤ 2.5 times the upper limit of normal
- Serum creatinine level ≤ 2 times the upper limit of normal
- Complete blood count with hemoglobin level of at least 7.0 g/dL
- Complete blood count with platelet count of at least 50,000/mm3
- Serum potassium ≥ 3.5 meq/L
- Negative pregnancy test (women of childbearing potential)
  - 1. Exclusion Criteria

1. Breast-feeding
2. Known intolerance to any of the study drugs
3. Known allergy to any fluoroquinolone antibiotic
4. Concomitant disorders or conditions for which moxifloxacin (MXF), isoniazid (INH), rifampin (RIF), pyrazinamide (PZA), or ethambutol (EMB) are contraindicated. These include severe hepatic damage, acute liver disease of any cause, and acute uncontrolled gouty arthritis.
5. Current or planned therapy during the intensive phase of therapy using drugs having unacceptable interactions with rifampin (rifabutin can be substituted for rifampin during the continuation phase of therapy)
6. Current or planned antiretroviral therapy during the intensive phase of therapy
7. History of prolonged QT syndrome or current or planned therapy with quinidine, procainamide, amiodarone, sotalol, disopyramide, ziprasidone, or terfenadine during the intensive phase of therapy.
8. Pulmonary silicosis
9. Central nervous system TB
10. **STUDY PLAN**
    1. Study Procedures
       1. Screening Visit

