Pyrazinamide resistance – Isolated pyrazinamide resistance is extremely rare, except among *M. bovis* strains (*M. bovis* is characteristically resistant to pyrazinamide). Patients found to have confirmed pyrazinamide resistance or intolerance will be taken off their assigned study regimen and treated using an individualized regimen. Patients with pyrazinamide resistance or intolerance will not be included in the analysis of sputum culture conversion. Patients receiving study (intensive) phase therapy at the time of discontinuation of the study regimen will have a study visit at 2 weeks after discontinuation of the study regimen for assessment of delayed toxicity, and then will no longer be followed in the study. Patients receiving continuation phase therapy at the time of discontinuation will no longer be followed in the study.

Rifampin resistance, with or without resistance to other drugs – Patients having a rifampin-resistant isolate or rifampin intolerance will be taken off their assigned study regimen and treated using an individualized regimen. Patients with rifampin resistance or intolerance will not be included in the analysis of sputum culture conversion. Patients receiving study (intensive) phase therapy at the time of discontinuation of the study regimen will have a study visit at 2 weeks after discontinuation of the study regimen for assessment of delayed toxicity, and then will no longer be followed in the study. Patients receiving continuation phase therapy at the time of discontinuation will no longer be followed in the study.

Ethambutol resistance – Rates of ethambutol resistance are low in Uganda[110], Canada[111], and the United States[109]. The study regimen should be very active for a patient having an ethambutol-resistant isolate. These patients will be kept on their assigned study regimen and included in the analysis of sputum culture conversion.

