In general, for grade 1 toxicities, the patient will be followed carefully and the study drugs will be continued. For grade 2 toxicities, the patient will be followed more carefully, with additional laboratory and/or clinic visits as necessary, and the study drugs temporarily held at the investigator's discretion. For any grade 3 toxicity that, in the principal investigator’s judgment is due to study drug(s), the causative study drug(s) should be held. The clinician should rule out other possible causes of the symptoms before discontinuing study medication. When possible, concomitant medications should be held first at the discretion of the principal investigator if he/she suspects they are contributing to the toxicity. Depending on the nature and severity of the toxicity, the degree to which it resolves, and/or the emergence of alternative explanations for the toxicity or the subject’s deterioration, the study drugs(s) may be restarted at the discretion of the investigator. For any recurring grade 3 or grade 4 toxicity, the study drugs should be temporarily held and may be permanently stopped at the discretion of the investigator.

Any patient with grade 4 renal, hepatic, cardiac or hematological toxicity will be immediately discontinued from study therapy. The laboratory test or clinical finding in question will be reassessed as soon as possible. The repeat test will guide management of the event as follows:

- If the repeat assessment shows toxicity of grade 3 or lower, and if the patient has continued to receive study drugs between the two testing dates, then the patient will be managed according to the appropriate toxicity level of the repeat test.
- If the repeat test shows toxicity of grade 3 or lower, and if the patient has not received study drugs between the two testing dates, then the patient will be managed at the discretion of the investigator with regard to the re-administration of study drugs, and otherwise according to the toxicity level of the repeat test.
- If the repeat test shows grade 4 toxicity, then the patient will be permanently discontinued from study medications. Further treatment of TB will be directed by the investigator on an individualized basis. The patient will continue to be followed for study monitoring purposes (as are other patients who make a permanent departure).

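### Section 5.2 applies its baseline-resistance rules to rifampin and pyrazinamide intolerance, which contradicts 5.5 and 5.6 on follow-up and, for a narrower group, 6.1 on the conversion analysis

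*Protocol*

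**What the plan says.** Section 5.2 concerns patients whose baseline isolate is drug-resistant. Two of its paragraphs go further. The rifampin paragraph states: "Patients with rifampin resistance or intolerance will not be included in the analysis of sputum culture conversion". The pyrazinamide paragraph states: "Patients with pyrazinamide resistance or intolerance will not be included in the analysis of sputum culture conversion". The isoniazid, fluoroquinolone and ethambutol paragraphs do not mention intolerance.

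In both paragraphs, a patient stopped during the intensive phase has one visit two weeks later "for assessment of delayed toxicity, and then will no longer be followed in the study". For later stops: "Patients receiving continuation phase therapy at the time of discontinuation will no longer be followed in the study".

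Elsewhere the Protocol says something different about stops for toxicity:

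- **5.5**, on confirmed grade 4 renal, hepatic, cardiac or hematological toxicity: "The patient will continue to be followed for study monitoring purposes (as are other patients who make a permanent departure".
- **5.6** provides continued study follow-up on a non-study regimen "for patients in whom treatment-emergent drug toxicity warrants discontinuation of study therapy, and for patients who become pregnant", and adds: "These patients will be followed in the study for a maximum of 6 months of TB treatment".
- **6.1** lists five exclusions from the conversion analysis. They include baseline resistance and more than 14 days of non-study therapy in the intensive phase. Intolerance is not among them.

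**The concern.** Resistance of the baseline isolate is fixed before randomization. Intolerance is an event after it. By handling both in the same sentences, 5.2 gives a site two incompatible instructions for one patient and gives the analyst two definitions of the primary analysis set.

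Two things are at stake. First, a patient may be dropped from the primary comparison because of a post-randomization event, in some cases after the endpoint has been observed. Second, scheduled follow-up ends for patients who have had toxicity, although delayed toxicity and treatment failure are stated secondary objectives. An SAP can settle the first. It cannot recover visits that sites, following the Protocol, did not hold.

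**Working it through.** The point is textual, and no figure in the plan is in dispute.

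**1. Is intolerance a post-randomization event here?** The exclusion criteria include "Known intolerance to any of the study drugs". Section 3.2, discussing isoniazid, likewise says that known intolerance prevents enrolment but that intolerance may develop during therapy. So intolerance in an enrolled patient is normally treatment-emergent. Section 5.2 does not define the term.

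**2. Follow-up, side by side.**

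| Patient stopped for rifampin or pyrazinamide intolerance | Under 5.2 | Under 5.5 and 5.6 |
| --- | --- | --- |
| Intensive phase | One visit at 2 weeks, then none | Stays on study, up to 6 months of TB treatment |
| Continuation phase | None | Same |

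Both columns cannot apply to one patient.

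**3. What the shorter follow-up loses.** On the nominal 8-week schedule, the latest intensive-phase stop is at week 8 and the last 5.2 visit is at week 8 + 2 = 10. The delayed-toxicity assessment in 4.1.4 is at month 3 (week 12 in the synopsis laboratory schedule). Treatment failure in 3.5 needs a positive culture after 4 months. Neither can be observed at scheduled visits in a patient released at week 10.

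**4. Analysis set: where 5.2 and 6.1 actually differ.**

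- *Early intensive phase.* The phase nominally lasts 8 × 7 = 56 days. A patient permanently moved to non-study therapy before about day 56 − 14 = 42 exceeds the 14-day limit and is out under 6.1 as well. Section 3.1 also requires the 40 or 44 doses to be completed within 54 to 70 days. There is no conflict for these patients.
- *Late intensive phase, after about day 42.* At most 14 days of non-study therapy remain, so 6.1 does not exclude and 5.2 does. Whether 3.1 excludes depends on whether substitute doses count toward the 40 or 44, which the Protocol does not say.
- *Continuation phase.* The doses are complete and both end-of-phase cultures may have been taken. Sections 3.1 and 6.1 then keep the patient, while 5.2 read literally removes the patient after the endpoint is known. This is chiefly a rifampin case, since 3.2 lists pyrazinamide in the continuation phase only for patients intolerant of isoniazid.

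**5. Size: illustration only.** The planned 205 per arm follows from 154/(1 − 0.25) = 205.3. The only discontinuation rates in the Protocol that could serve as a ceiling are in Table 6: any drug permanently stopped in 11.5% and 8.1% of patients in an earlier levofloxacin trial. An assumed range of 2% to 11.5% gives 205 × 0.02 = 4.1 to 205 × 0.115 = 23.6 patients per arm. That is a ceiling for the follow-up conflict, and too high for the analysis-set conflict because of step 4.

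For bias, suppose true conversion is 75% in both arms, a fraction *e* is excluded, and conversion among those excluded is *c*. The observed rate is (0.75 − *e·c*)/(1 − *e*).

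| Exclusions, arm 1 vs arm 2 | *c* | Observed rates | Spurious difference |
| --- | --- | --- | --- |
| 10% vs 5% | 30% | 0.720/0.90 = 0.800; 0.735/0.95 = 0.774 | 2.6 points |
| 11.5% vs 8.1% | 30% | 0.7155/0.885 = 0.808; 0.7257/0.919 = 0.790 | 1.9 points |
| 10% vs 5% | 60% | 0.690/0.90 = 0.767; 0.720/0.95 = 0.758 | 0.9 points |

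The sign reverses if the arms are swapped, and the difference is zero if exclusions and *c* are equal across arms. All rows assume that 5.2 alone causes the exclusion.

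**The case against.** Four points can be made on the other side.

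- **The safety data are not lost.** A reader might infer that treatment-related events leave the trial. They do not. Section 6.1 puts all randomized patients in the toxicity analyses, the tolerability endpoint in 3.5 counts discontinuation for any reason, 5.4 requires reporting of drug discontinuation and grade 3 or 4 toxicity, and 5.3 repeats tests until a toxicity resolves or stabilizes. This stands. What is lost is later scheduled follow-up, plus the conversion outcome of the patients in the narrower group.
- **Most early cases are out anyway.** This also stands, and it limits the analysis-set conflict as in step 4. It does not touch the follow-up conflict.
- **Post-randomization exclusion is a declared choice.** Section 6.1 says it follows the British Medical Research Council procedure. Granted; the principle is not challenged here. But that declared list does not contain intolerance, so 5.2 adds an exclusion that the list does not declare.
- **Nothing shows that intolerance differs by arm.** Rifampin and pyrazinamide are in both regimens. A reader might infer a difference from the background section on rifampin/pyrazinamide toxicity, which mentions a possible mitigating effect of isoniazid. That section offers it as one of several possible explanations and says the mechanism is unknown. Table 6 shows fewer stops with levofloxacin, but isoniazid was in both arms there. A difference is possible and not established.

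One could also argue that a continuation-phase patient has no assigned regimen left to stop. Section 5.2 nevertheless addresses such patients explicitly, and its analysis sentences carry no time limit.

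**Conclusion.** The contradiction is real and should be corrected. On follow-up it affects all patients stopped for rifampin or pyrazinamide intolerance (other than those who withdraw consent), at the cost of month 3 toxicity and treatment-failure data. On the analysis set it affects only those whom 3.1 and 6.1 do not already exclude: arguably some late intensive-phase cases, and clearly continuation-phase cases whose endpoint cultures were already obtained.

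It would go too far to read Table 6 as showing that 17 to 24 patients per arm (205 × 0.081 = 16.6; 205 × 0.115 = 23.6) change status, or to quote 2.6 points as the bias. The Protocol gives no intolerance rate for either drug, no conversion rate among intolerant patients and no evidence of a difference between arms. Those figures are upper assumptions, and the size and direction of any bias are unknown. Nor do 5.5 and 5.6 settle the analysis set: they govern follow-up only.

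**What to change.** In the rifampin and pyrazinamide paragraphs of 5.2:

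1. Delete *or intolerance* from the two sentences on the conversion analysis, so that 6.1 (with the completion window in 3.1) alone decides inclusion.
2. Limit the four end-of-follow-up sentences, two per paragraph, to patients with baseline resistance. These sentences do not contain the word intolerance; they inherit it from the sentences before them. Step 1 alone would therefore leave the follow-up conflict in place.
3. Add one sentence stating that patients discontinued for intolerance are followed as in 5.5 and 5.6.

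The cost is four deleted words, a short qualifier in four sentences and one new sentence. The visits retained for the patients concerned are those that 5.6 already provides. Nothing here bears on how or whether these patients are treated.
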